### 2.4. Recruitment

Participants will be recruited using several approaches including (a) distribution of recruitment material through early childhood education and care services and playgroups using existing networks; and (b) social marketing and targeted advertisements through online social networks, such as Facebook and online parenting forums. A study flyer, including brief information about the study and a link to the study website, will be used to distribute study information to parents through the above networks. The website provides comprehensive information about the study, including eligibility criteria, and includes a link to the baseline online survey (developed using Lime Survey). Consenting parents will need to complete the online consent form before they can proceed to the survey questions. Recruitment of participants will continue until a sample of at least 50 participants is obtained. As a thank-you for their time and participation, all participants will receive a $20 retail voucher after completing their 6-week post-intervention questionnaire.

### 2.5. Randomisation, Allocation and Blinding

After the baseline survey is completed, participants will be randomly allocated to the intervention or the control groups in a 1:1 ratio using computer-generated block randomization schedule by a researcher not involved in data collection or recruitment, to facilitate equal group allocation. Because of the type of intervention used in this trial, participants cannot be blinded to group allocation.

### 2.6. Intervention

Triple P is a multilevel parenting and family support strategy developed by researchers at the University of Queensland, Australia. Self-regulation is the central construct of Triple P. The system takes a social learning approach to support healthy child development as well as to prevent and manage behavioural, social and emotional problems in children [31]. The intervention content focuses on reciprocal and bidirectional patterns of parent-child interaction and emphasizes positive and responsive parenting practices [38]. Parents are prompted to set up developmentally appropriate goals, have realistic expectations, create a safe, engaging and positive learning environment for children and use assertive discipline. The program is embedded within a self-regulatory framework which comprises a number of factors including self-sufficiency, self-efficacy and self-management, and is derived from social cognitive theory [39]. Further, parents’ capacity to monitor their own behaviour and that of their child is fundamental to achieving positive intervention outcomes [31].

Healthy Habits Triple P, tested in this study, is an online, self-directed intervention to help parents develop effective parenting practices and increase their confidence in managing children’s eating and mealtime behaviours. The intervention consists of two modules. Module 1 consists of eight sections covering evidence-based positive parenting strategies in the context of developing healthy habits with young children, including strategies for encouraging healthy habits (e.g., having realistic expectations and use of specific instructions, praise, reward charts and routines), dealing with resistance, planning for high-risk situations, building children’s independence, parental coping and using evidence to make informed decisions about children’s health. Module 2 has four sections focusing on the application of positive parenting strategies to eating and mealtime behaviours (e.g., encouraging healthy food choices, increasing food variety, encouraging self-regulation and dealing with problem eating and mealtime behaviours). This section focuses on formulating individual parent- or child-focused goals and applying relevant parenting strategies to reach these goals. The intervention takes approximately 4–5 hours to complete, with parents encouraged to complete the modules over a two-week period. Module content is tailored towards key concerns and difficulties commonly experienced by the parents of young children. The modules include psychoeducation alongside the text, audio and videos guiding parents in the use of specific parenting techniques. The intervention has been developed to engage parents by including narratives and examples to help parents relate the material to their own lives.

### 2.7. Data Collection

All data will be collected using validated parent-reported questionnaires that are to be completed online. Parents will complete the baseline survey soon after recruitment into the study and the post-intervention survey 6 weeks after randomization. Both the baseline and post-intervention surveys will be hosted on the Lime Survey platform. In order to minimize attrition, email reminders will be sent to parents to complete the modules and the post-intervention survey. The prompts will be sent out on a weekly basis after the participants are randomized. Additional reminders will be sent to families where post-intervention assessments have not been completed by the due date. The control group will complete the same set of assessments at the same time points.

Family socio-demographic information will be collected at baseline using the Family Background Questionnaire [40], including the child’s age, sex, postcode, the relationship of the respondent to the child, marital status, family structure, ethnicity, number of people living in the house, level of education, work status and country of birth of the respondent and their partner and the family’s ability to meet essential expenses.

### 2.8. Primary Outcomes

The efficacy of the intervention will be measured through parent-reported changes in children’s diets using the validated Children’s Dietary Questionnaire (CDQ) [41]. The CDQ is a 28-item questionnaire that assesses children’s dietary intake patterns over the past week (or 24 h) for foods and beverages which are recommended or discouraged for health reasons. The tool was developed based on the Australian healthy eating guidelines and has demonstrated acceptable reliability and validity for assessing dietary patterns among preschool children at a population level [42]. It has been recommended for use in evaluating the efficacy of interventions to improve children’s eating habits [42]. All subscales of CDQ had Cronbach’s alpha (α) values of ≥0.6 [42].

### 2.9. Secondary Outcomes

Parents’ confidence in dealing with children’s demands for sugar-rich foods will be assessed using the Comprehensive Snack Parenting Questionnaire (CSPQ). The CSPQ is a parent-reported questionnaire comprising 21 items with a five-point Likert response scale ranging from ‘strongly disagree’ to ‘strongly agree’ [43]. In an Australian study with 134 participants, the Cronbach’s α value of the total scale was 0.752 [44]. In addition, parents’ self-efficacy for promoting healthy eating and limiting non-core foods will be evaluated using nine items from a previous Australian study [45]. Self-efficacy for promoting healthy eating is measured by five items assessing parents’ confidence in their ability to get their child to eat healthily (e.g., “How confident are you that you could get your baby/child to eat enough fruit over the next year?”) and a further four items assess parents’ confidence in refusing their child’s requests for unhealthy/non-core foods (e.g., “How confident are you that you could say no to your baby/child’s demands/fussing for sweet snacks, confectionary, lollies and/or ice cream?”). The responses are rated on a five-point Likert scale ranging from ‘not confident at all−1′ to ‘very confident−5′, with higher scores indicating higher levels of self-efficacy. The self-efficacy scale was found to be reliable (α = 0.86) [43].

Lastly, parents will complete the child feeding behaviour and mealtime parenting strategies scales of the Parent and Toddler Feeding Assessment (PATFA), a parent-report questionnaire used to assess child behaviour, parenting confidence and parenting strategies relevant to child feeding and mealtimes [46]. Parents will be asked to rate the frequency of 16 common child feeding problems (e.g., spitting food out) on a five-point scale from 1 (never) to 5 (almost always) and whether each behaviour was problematic (yes/no), followed by their confidence in managing each behaviour on a 10-point scale (with higher scores indicating greater confidence). Parents will also rate how frequently they used each of 29 parenting strategies at mealtimes (e.g., eating with the child) on a five-point scale from 1 (never) to 5 (almost always). The subscales of PATFA have good test–retest reliability (*r*  =  0.68–0.89) and excellent internal consistency (α  =  0.65–0.97).

### 2.10. Practicality and Acceptability

Practicality will be assessed by determining the rate of completion (number of participants accessing and completing all the modules of the intervention) and data collected remotely from the online intervention platform. Time required to recruit the estimated sample will also be estimated [47].

Acceptability of the intervention will be assessed both through open-ended questions and qualitative interviews. The three open-ended questions, such as “Do you have any other comments about the program or any suggestions about how we could improve the program for families in the future”, will help evaluate the perceived usefulness of online modules. Personal interviews will also assist in obtaining parents’ perception of the usefulness of the content, barriers and facilitators of using the intervention. We will evaluate parents’ satisfaction with the intervention using the Client Satisfaction Survey [48]. The survey consists of 10 items which are rated using a seven-point Likert response scale (e.g., “Has the program helped you to deal more effectively with your child’s eating or mealtime behaviour?”)

### 2.11. Quantitative Data Analysis

Quantitative data from this pilot study will be descriptive, with outcomes being interval estimates of variables relating to children’s dietary habits, parenting and child behaviours and parenting efficacy. Data will be de-identified, and SPSS (Version 27.0. Armonk, NY, USA: IBM Corp) will be used to conduct data analysis. Data will be examined for outliers and missing values. All data will be analyzed based on the intention to treat (ITT) principle. To account for repeated measurements, two-way repeated-measures ANOVAs will be used to evaluate changes in diet and other study outcomes between the intervention and control groups.

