A recent systematic review by Gomes et al. (2021) found that, despite a growing body of research examining the effects of parent-focused web-based interventions to promote children’s healthy diet, there is a paucity of studies examining the effects on parental feeding practices [23]. There is emerging evidence of web-based interventions improving parents’ knowledge, behaviour and attitudes in the context of child obesity and overweight [24,25]. Although most of the web-based interventions were theory-driven and included standard behaviour change techniques (e.g., instruction and demonstration of parenting behaviours) [26,27], few included strategies, such as the identification of oneself as a role model [28], promotion of children’s self-regulation or the management of parents’ emotional responses to children’s eating challenges, all of which are important to the development of healthy eating behaviours in childhood [29].

As a public health priority, government agencies recommend using primary and secondary prevention strategies to minimize the burden of diseases and associated risk factors [30]; however, despite these recommendations, a majority of parenting interventions for childhood obesity and overweight are treatment-based rather than prevention-oriented [25]. The Triple P (Positive Parenting Program) is a multi-level, prevention-oriented program, based on social learning principles and grounded in a self-regulatory framework, that takes a minimal sufficiency approach to support the development of parent and child self-regulation [31]. It aims to enhance parents’ knowledge, skills and confidence; promotes positive and nurturing environments; teaches strategies to support healthy child development and manage children’s problem behaviours; and supports parents with self-care and managing their own stress [32]. All of these factors have been identified as important to the development of healthy eating and mealtime behaviours in childhood [23]. The aim of this trial is to examine the efficacy of a prevention-based online intervention (Healthy Habits Triple P) designed to support parents to develop healthy eating and mealtime behaviours with their young children (2–6 years) in Australia.

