### 2.1. Design

The proposed study is a randomized controlled trial to assess the efficacy of a web-based parenting support program for promoting healthy eating and mealtime behaviours. There will be two data collection time-points: baseline and post-intervention (6 weeks after the intervention). All participants in the intervention group will receive the web-based Healthy Habits Triple P intervention. The control group, on the other hand, will only have access to the online intervention after completing the six-week follow-up assessment. All parents will receive a brochure on child nutrition, produced by the Australian government (National Health and Medical Research Council (2021)) [34].

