### 2.3. Sample Size

In this trial, following the recommendations of Whitehead et al. (2016), a sample size of 15 families per arm will be required with 90% power and two-sided 5% significance [35] and medium effect size (Cohen’s d = 0.5) based on meta-analysis of the effects of the Triple P on parenting and child outcomes [36]. Allowing for an attrition rate of 60%, 25 participants will be recruited to each arm. We have allowed for an attrition rate of 60%, which is greater than the traditional 20% attrition rate commonly used in trials of public health interventions. Participant anonymity in this study may contribute to reduced rates of assessment completion post-intervention [37]. An increase in sample size by 60% will ensure that sufficient sample size is retained.

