## 3. Discussion

This study will examine the efficacy of Healthy Habits Triple P, an online intervention developed to improve children’s snacking and mealtime behaviours and related parenting practices. Healthy Habits Triple P has been developed in response to research identifying parents as important for behaviour maintenance and behaviour change in relation to their children’s snacking and mealtime behaviours [49]. Interventions that aim to alter the child’s eating behaviours often focus on parents as a proximal influence [50]. Prior interventions have varied in content, such as programs that seek to increase parental awareness of their child’s obesity risk [51], encouraging regular family routines around mealtimes, sleep, and/or media use [52], and family-based obesity prevention strategies that seek to engage the whole family unit [53] or intervention approaches that focus more directly on parents’ own weight management and nutrition [54].

Online administered, preventive public health interventions addressing lifestyle-associated disease risk factors could be cost-effective and could easily be scaled up. A recent systematic review by Gomes et al. (2020) evaluated the effectiveness of web-based interventions in changing parental feeding practices [23]. The review demonstrates that several intervention elements that are central to social cognitive theory, such as ‘*goals and planning*’ and ‘*feedback and monitoring*’, have been infrequently incorporated into interventions to date [26]. There is also evidence that healthy eating and physical activity interventions that combine self-monitoring with at least one other self-regulatory strategy tend to be more effective than programs that do not include these elements [55]. Healthy Habits Triple P builds upon previous research in this area by incorporating important drivers of behaviour change, including ‘goal setting’, ‘monitoring of parent and child behaviour’ and parent ‘self-reflection’. It aims to develop parents’ capacity for self-regulation as a central skill, resulting in parents becoming independent problem solvers and being able to implement parenting strategies effectively.

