The systematic review by Gomes et al. (2020) also found that most parent-focused web-based interventions did not improve diet-related parenting practices, except for food availability [23]. These negligible effects could be attributed to the inclusion of active control groups which, in many studies, received content that was overly similar to that provided to the intervention groups. In our trial, a waitlist control group will be used to maximize treatment separation and help prevent the problem of diluted effect, reported in previous studies.

It is important for parent-focused interventions: to acknowledge that each child has different choices and behaviours related to eating; to address parents’ own beliefs, attitudes and goals related to healthy eating; and to promote strategies to address other family factors, such as involving other caregivers [56]. Our intervention tailors to individual circumstances by helping parents to have realistic expectations of their child and themselves, given their child’s age and stage of development; to develop child-focused goals that are based on their own individual needs and priorities; and to develop and maintain effective daily routines by planning ahead and involving other family members.

One potential limitation of the study is the reliance on parent-reported measures for outcome assessment. However, at minimum, the results from this study will provide a good indication of whether an intervention such as this is practical to deliver and acceptable to parents. Future studies should explore the concordance of parent-reported parenting and child behaviour outcomes with observed measures of parent and child behaviour. This study provides the opportunity to estimate important study-specific parameters required to inform the design of future definitive controlled trials [57] which, if successful, will pave the way toward implementation as a preventive public health intervention within existing healthcare settings.

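### The article gives two purposes, efficacy trial and descriptive pilot, without saying which governs the conclusion; at the planned size a test-based efficacy verdict is not supported

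*Protocol article*

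**What the plan says.** The protocol article describes the study's purpose in two ways.

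- **Efficacy.** The Introduction states: "The aim of this trial is to examine the efficacy of a prevention-based online intervention". Section 2.1 states: "The proposed study is a randomized controlled trial to assess the efficacy of a web-based parenting support program". The Discussion opens with: "This study will examine the efficacy of Healthy Habits Triple P". The abstract and section 2.8 (Primary Outcomes) also speak of efficacy. Section 2.3 gives a hypothesis-testing rationale for the sample: "a sample size of 15 families per arm will be required with 90% power and two-sided 5% significance", at d = 0.5.
- **Pilot and estimation.** Section 2.11 states: "Quantitative data from this pilot study will be descriptive, with outcomes being interval estimates of variables". Section 2.10 plans completion rate, recruitment time and acceptability. The last paragraph of the Discussion says the study gives the chance to "estimate important study-specific parameters required to inform the design of future definitive controlled trials".

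Section 2.11 contains both. After the sentence on descriptive data it adds that "two-way repeated-measures ANOVAs will be used to evaluate changes in diet and other study outcomes between the intervention and control groups". The article does not call these ANOVAs exploratory, and it does not say that efficacy conclusions will be withheld.

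**The concern.** The same data can be reported in two ways: as a verdict on whether the programme works, reached through a test, or as an interval estimate with feasibility results that informs a later trial. A reader of the article cannot tell which one the investigators have committed to, and the choice could be made after the results are known.

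It matters because of the size of the trial. If the tests had the 90% power stated in section 2.3, the label would be of little consequence. If power is low, a non-significant result says little about the programme. A significant one tends to exaggerate the effect, in a study whose estimates are meant to help design the next trial.

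**Working it through.** **Inputs from the article**

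- Effect d = 0.5, two-sided 5%, 90% power, 15 families per arm, 25 per arm recruited, 60% attrition (section 2.3)
- At least 50 participants in total (section 2.4); 1:1 allocation (section 2.5)
- Two time points (section 2.1)
- Two-way repeated-measures ANOVA (section 2.11)

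**Assumption.** The correlation r between baseline and follow-up is not given, so results are shown over a range.

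**Step 1: the plan's own figure.** For a two-sample comparison,

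n per arm = 2 × (1.960 + 1.282)² / d² = 2 × 10.507 / 0.25 = 84.06, so 85 (86 with the t distribution).

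The stated 15 is not reproduced. One-sided 90% gives 69, two-sided 80% gives 63, one-sided 80% gives 50, and a one-sample or paired calculation gives about 42.

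**Step 2: the planned test.** With two time points, the group-by-time term of the ANOVA is the t-test on change scores. With an outcome SD of 1, the change has variance 2(1 − r). The noncentrality is therefore

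0.5 / √(2(1 − r)) × √(n/2), on 2n − 2 degrees of freedom.

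Example, n = 15, r = 0.5: 0.5 / 1 × √7.5 = 1.369 against a critical t of 2.048, giving power 26.2%.

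**Step 3: power over the range.** The rows are no loss (25), the stated requirement (15), and 25 less 60%, which is 25 × 0.4 = 10.

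| Completers per arm | r = 0.5 | r = 0.7 | r = 0.8 |
|---|---|---|---|
| 10 | 18.5% | 27.7% | 38.7% |
| 15 | 26.2% | 40.0% | 55.2% |
| 25 | 41.0% | 60.9% | 78.2% |

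Outside this range, 15 per arm gives about 16% at r = 0 and 84% at r = 0.9. Reaching 90% with 15 per arm needs 2(1 − r) = 15 × 0.25 / (2 × 10.507) = 0.178, so r is about 0.91.

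**Step 4: exaggeration of significant results.** The smallest observed effect that reaches significance is t × √(2/n) × √(2(1 − r)). At 15 per arm and r = 0.5 this is 2.048 × 0.365 × 1 = 0.75, already 1.5 times the assumed 0.5. By simulation of the change-score test at 15 per arm, the mean significant estimate is about 1.9, 1.5 and 1.3 times the truth at r = 0.5, 0.7 and 0.8.

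**Step 5: what the sample does give.** At r = 0.5 the half-width of the 95% CI for the standardised difference is 0.57 SD with 25 per arm, 0.75 SD with 15 and 0.94 SD with 10.

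**The case against.** The strongest objections, and what stands of each:

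- **The pilot purpose is not confined to section 2.11.** This stands. Only the word pilot is confined there; section 2.10 and the last paragraph of the Discussion already carry feasibility, acceptability and planning aims. A reader might infer that one stray sentence conflicts with an otherwise pure efficacy article, and that would be wrong. The mixture is wider, and no section resolves it.
- **ANOVA and interval estimates can coexist.** This also stands. The group-by-time term is a difference in change and can be given with a CI. Section 2.11 names no p-value or decision rule. The testing reading comes from joining the ANOVAs to the 5% level and power claim in section 2.3, which is the plainest sign of confirmatory intent.
- **A high correlation would rescue the test.** This stands in part. Power depends strongly on r, and with no loss at all r = 0.9 would give 97%. But the article assumes no correlation and itself allows for heavy attrition. The nearest figure, test–retest r of 0.68–0.89 for the PATFA subscales in section 2.9, belongs to a secondary scale and is not a six-week trial correlation. Even r = 0.8 leaves every row of the table below 90%.
- **The harm is speculative.** A reader might infer that a null result will be reported as no effect, or that the observed effect will size the next trial. The article says neither; the parameters it mentions could be the SD and retention. These are risks that the text leaves open.
- **Resizing for efficacy would also remove the conflict.** True, but it is a different trial: 85 completers per arm at 60% attrition means 85 / 0.4 = 212.5, so 213 recruited per arm.

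**Conclusion.** The point holds. The article states two purposes, and no section says which one governs the conclusion. At its own d = 0.5 and two-sided 5%, the planned comparison has between 18.5% and 78% power over 10 to 25 completers per arm and r from 0.5 to 0.8, against the 90% stated. A test-based efficacy verdict is therefore not supported, while estimation with intervals is.

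It would go too far to say that power is a quarter, or that significant estimates are 1.9 times too large, without qualification: both figures belong to 15 per arm and r = 0.5. Nor do the tests fail under all conditions. A true effect well above 0.5 (about 1.2 SD for 90% power at 15 per arm and r = 0.5), or r near 0.91, would be detectable, but the article assumes neither.

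The low power follows from the sample-size statement in section 2.3. If that statement is corrected as a separate matter, the power shortfall should not be counted twice; the conflict of purpose would still need resolving.

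**What to change.** Keep the sample at 50 and make the purpose consistent:

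1. State the pilot and estimation purpose in the abstract, the aim in the Introduction, sections 2.1, 2.8 and 2.11, and the Discussion.
2. Withdraw the 90% power claim in section 2.3, or restate the sample as a pilot number with the expected CI width. Changing the other sections alone would leave the article still claiming confirmatory power.
3. In section 2.11, make the baseline-adjusted between-arm difference with its 95% CI the main result in place of ANOVA significance tests, and report the outcome SD and retention with CIs. This uses data already collected. With 15 per arm, power after adjustment is 33% / 46% / 60% at r = 0.5 / 0.7 / 0.8, against 26% / 40% / 55% for the change comparison.
4. State that no efficacy conclusion will rest on p-values, and that the point estimate alone will not size the definitive trial.

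The cost is wording and a small change of analysis. Recruitment and data collection stay as they are. The real price is that the sponsor gives up a confirmatory efficacy claim.

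### Intention to treat is promised, but the named repeated-measures ANOVA, as written, uses only parents with both surveys and does not adjust for baseline

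*Protocol article*

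**What the plan says.** Section 2.11 sets the principle: "All data will be analyzed based on the intention to treat (ITT) principle". It then sets the method: "two-way repeated-measures ANOVAs will be used to evaluate changes in diet and other study outcomes between the intervention and control groups". On incomplete data it says only that "Data will be examined for outliers and missing values". No imputation, likelihood-based model or sensitivity analysis is named.

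Section 2.1 fixes the number of measurements: "There will be two data collection time-points: baseline and post-intervention". Section 2.5 places randomisation after the baseline survey, so every randomised parent has baseline data. Section 2.3 says "Allowing for an attrition rate of 60%, 25 participants will be recruited to each arm" and links the expected loss to parents not completing the post-intervention assessment. Section 2.4 sets recruitment at 50 or more.

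**The concern.** The principle and the method pull apart. Intention to treat implies that all randomised parents count in the comparison. A repeated-measures ANOVA on two time points needs both values, so a parent with a baseline survey only contributes nothing unless the missing value is first imputed. The missing survey is the very loss that section 2.3 expects on a large scale.

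A second weakness lies in the same choice of method. The group-by-time test compares raw changes and does not condition on the baseline score. That costs precision in a very small trial. It also lets baseline differences between the retained groups enter the effect estimate through regression to the mean.

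At stake are the meaning of the intention-to-treat label and the quality of the interval estimates that section 2.11 promises and that the Discussion wants to use for planning a definitive trial.

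**Working it through.** **1. How many parents the method leaves out**

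Inputs: 15 required and 25 recruited per arm, attrition 60% (section 2.3); 50 in total (section 2.4).

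The plan's own inflation:
- 15 × (1 + 0.60) = 24, close to the stated 25 and in line with its wording of a 60% increase.
- 15 / (1 − 0.60) = 37.5, so 38. This does not give 25.
- 15 / (1 − 0.40) = 25 exactly. So 25 per arm in fact covers 40% loss.

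Parents without follow-up:

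| Reading of the loss | Left out of 50 | Complete pairs | Per arm |
|---|---|---|---|
| 60%, as stated | 50 × 0.60 = 30 | 20 | 10 |
| 40%, as the inflation implies | 50 × 0.40 = 20 | 30 | 15 |

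The mismatch between 60% and 25 per arm is a separate sample-size matter. Here it only sets the range.

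**2. What the method estimates**

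Let B be baseline and F follow-up. With two groups and two times, the group-by-time F statistic is the square of the two-sample t statistic on F − B. A parent without F has no F − B.

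**3. Precision**

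Assume SD 1 at both times and correlation ρ. The documents give no value for ρ.
- Variance of the change score: 2(1 − ρ).
- Residual variance after adjusting for baseline: 1 − ρ².
- At ρ = 0.6: 2 × 0.4 = 0.80 against 1 − 0.36 = 0.64, a fifth lower.
- At ρ = 0.7: 2 × 0.3 = 0.60 against 1 − 0.49 = 0.51.

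Standard error of the arm difference at ρ = 0.6, with n complete pairs per arm, is √(2 × variance / n):
- n = 10: √(2 × 0.80 / 10) = 0.40 for change, √(2 × 0.64 / 10) = 0.36 adjusted.
- n = 15: √(2 × 0.80 / 15) = 0.33 for change, √(2 × 0.64 / 15) = 0.29 adjusted.

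**4. Bias under selective retention**

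Suppose there is no true effect and retention depends only on B. If the retained intervention parents differ from the retained control parents by δ in mean baseline, the change-score contrast is (ρ − 1) × δ. An analysis that conditions on B has no such term.

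Illustration: 41% retained in each arm. Retention is logistic in B in the intervention arm only and random in the control arm. Integrating over a standard normal baseline gives δ:

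| Odds ratio of retention per SD of baseline | δ | Bias at ρ = 0.6 | Bias at ρ = 0.7 |
|---|---|---|---|
| 1.5 | 0.23 | −0.4 × 0.23 = −0.09 | −0.3 × 0.23 = −0.07 |
| 2.0 | 0.37 | −0.4 × 0.37 = −0.15 | −0.3 × 0.37 = −0.11 |
| 2.7 | 0.49 | −0.4 × 0.49 = −0.19 (unrounded δ) | −0.3 × 0.49 = −0.15 |

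The sign follows from the assumed direction of selection. If the same dependence holds in both arms, δ = 0 and the bias is about zero. The odds ratios and correlations are assumptions. The documents supply neither.

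**5. Which defect causes the bias**

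An ANCOVA restricted to complete pairs drops exactly the same parents and has bias of about zero in this scenario. The bias in step 4 therefore comes from not conditioning on baseline, not from the exclusion itself.

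**The case against.** The strongest reply is that the conflict is one of wording. Repeated-measures ANOVA can be run on imputed data and then keeps every randomised parent. The article condenses a fuller plan, and imputation rules are often left to the analysis plan. This stands in part. A reader might infer that the named method can never deliver intention to treat, and the documents do not support that. What remains is that the article fixes the principle and the method side by side, names nothing that joins them, and expects heavy loss of the one measurement the method cannot do without.

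A reader might also infer that attrition will differ by arm, because control parents "will only have access to the online intervention after completing the six-week follow-up assessment" and so have an extra reason to return the survey. That is plausible but not shown. Section 2.4 offers all participants a $20 voucher after the 6-week questionnaire, and section 2.7 provides weekly prompts and extra reminders for overdue surveys. No retention figures by arm are given.

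Thirdly, section 2.11 calls the study a pilot with descriptive results. That lowers the stakes, but sections 1, 2.1 and 3 also claim to examine efficacy, and a biased or imprecise interval estimate serves neither purpose. Nor is the illustrated bias large against the noise: with 10 pairs per arm the standard error of about 0.40 SD is roughly twice the largest bias shown.

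**Conclusion.** The concern holds in a limited form. As written, with no imputation stated, the analysis is a change-score comparison of completers carrying an intention-to-treat label. It leaves out 30 of 50 parents at the stated attrition, or 20 of 50 on the 40% reading.

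The failure to adjust for baseline is a real and separate cost. Precision is lost for certain, to a degree that depends on the correlation. Bias arises only if retention depends on baseline differently in the two arms. The figures of about −0.09 to −0.19 SD at a correlation of 0.6 show what could happen and are not a forecast. They should not be read as the effect of dropping parents.

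This should be fixed before analysis. It does not invalidate the design.

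**What to change.** Replace the repeated-measures ANOVA in section 2.11 with a baseline-adjusted estimate of the 6-week arm difference and its confidence interval. A likelihood-based mixed model in SPSS, fitted to all randomised parents with the baseline mean constrained equal across arms, does this. ANCOVA after multiple imputation has the same aim.

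The text should also say:
- that the estimate assumes follow-up is missing at random given the data in the model;
- that the model does not recover lost follow-up information. With two time points, parents with baseline only have little influence on the 6-week contrast, and the main gain is the adjustment for baseline;
- that one sensitivity analysis will shift the missing follow-up values by stated amounts.

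If repeated-measures ANOVA on complete pairs is kept, call it a completers analysis and do not label it intention to treat.

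The cost is revised wording and a little more analysis work in the software already named. No further data are needed.
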